There is a specific lack of knowledge on the impact of knowledge transfer on complex clinical decision-making. The majority of intervention trials attempting to change clinical behavior have focused on the prescribing practices of physicians, limiting the generalizability to clinical practices used to manage chronic musculoskeletal or childhood disability problems. Management of chronic conditions requires that health care professional deal with multi-factorial disability issues by selecting multi-level customized interventions. It is more difficult to assess how KT impacts on clinical decision-making in this situation, as compared to monitoring adherence to prescription recommendations. Beggs and Sumison [37] presented a model that incorporated multi-level evaluation of the long-term benefits of continuing education within a Northern Outreach Program for PT and OT. They proposed a 4-stage model of evaluation. Stage 1 involves participant evaluation of the event. Stage 2 evaluates the affective, cognitive, and psychomotor changes that participants experience as a result of the event; this typically requires a pre-test and post-test of attitudes, knowledge, or specific skills. In Stages 3 and 4, higher levels of evaluation are incorporated. Stage 3 evaluates the extent to which programs change the behavior of the clinician within their practice and requires chart audits and observations. Stage 4 focuses on the client and requires evaluation of the efficiency, effectiveness, adequacy and appropriateness of care and its impact on resultant health outcomes.

We know from surveys of orthopedic practice [18] that the use of standardized health outcome measures is low. Conversely, within pediatric rehabilitation utilization levels are higher, but therapists reported difficulty in selecting and applying available outcome measures appropriately (pilot work, publication under review). It is clear that evaluation of knowledge transfer should measure changes in knowledge, intent, and behavior, but also determine how new knowledge is incorporated into clinical decision-making.

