#### Sample size requirements

Given that this study is a mixed-methods design, the sample size was based on the quantitative analyses as these have larger sample size requirements. Sample size estimation was based on detecting an effect of 0.50 between groups on any of the three aspects of outcome (knowledge, utilization, and integration into clinical reasoning). Assuming Type I error = 0.05 (2-tailed); Type II error = 0.80; Effect size = 0.50, the sample size required per group = 64. The sample size required for two-comparison groups = 128 and accounting for a 10% dropout = 128/0.9 = 142. We anticipate low dropouts given the priority of continuing education by both professions. We will round our sample size up to 144 to provide a number equally divided between three sites, requiring 48 per site. Based on the need to allocate participants in blocks to interventions and to balance professions and clinical areas evenly, we expect to accommodate 24 participants per intervention group, per site. These will consist of three tutorial groups of eight therapists/groups. Given the distribution of practice patterns in rehabilitation, we expect two groups on orthopedics and one group on pediatric practice at each location. Groups will be formed according to practice settings to insure that the stakeholders can develop "problems" that simulate their own clinical settings/populations.

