#### Group assignment procedure

A randomized design is usually the most rigorous, allowing for control of known and unknown confounders. In this case, it is not the most appropriate design strategy and we have selected a quasi-experimental approach. Research design methodologists have indicated that attaining an equal distribution of confounders in small samples via randomization, such as that required for the present study, is unreliable. Therefore we will use a non-randomized allocation procedure called minimization, which places participants in intervention groups to minimize the differences across key predictors [69-71]. We have identified pre-test scores, years of practice, practice area (urban/rural), and practice type (PT/OT) as the key predictors. Minimization across key predictors will balance prognostic variables and result in more valid comparisons [71]. Subjects will be allocated using minimization within orthopedic and pediatric groups at each site. At each site the pool of subjects will be allocated minimizing difference by: creating pair groupings based on professional training (PT/OT), matching area practice and then most similar pre-test scores, and, finally, by minimizing years of practice. We then will conduct descriptive analyses of group similarities and test whether we can optimize groups' consistency by reallocation of assignment. When this process is complete, subjects at each site will be informed of their assignment.

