The chart-stimulated recall will be conducted by a single trained research assistant assigned to each location. Two of the five charts selected for chart audit will be randomly selected for chart-stimulated recall. The interviewer will ask questions in a semi-structured format that requires specific responses from the therapist, explaining the content and clinical reasoning used for the two patients whose records are used to evaluate the core competencies being tested. The answers are scored on a seven-point scale. The spectrum of information included in the chart-stimulated recall analysis will include all intake assessments, progress notes, and discharge records for a specific patient. A detailed manual on the types of responses required will be developed in conjunction with curriculum development. Chart-stimulated recall will provide a quantitative assessment of the clinical reasoning used with respect to the use of outcome measures in managing specific patients.

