## Analyses

### Quantitative analyses

All data will be double-entered in SPSS 14.0. Descriptive analyses will be conducted, including checking for outliers, normality testing, and univariate correlations. The first primary analysis (Objective 1) will be a two-way repeated measures analysis of variance to determine primary unadjusted differences in absolute scores over time, and between groups for each of the three primary outcome measures: knowledge, utilization, and chart-stimulated recall scores. An analysis of covariance will be used to compare these same effects adjusting for baseline knowledge score, Readiness to Change, years of practice, and educational preference. These analyses across the e-PBL and SHIPS groups will determine the relative effectiveness of these two alternative knowledge transfer choices. Effect sizes and their 95% confidence intervals will be calculated to determine whether there are differential impacts on change in knowledge, utilization, and integration of knowledge between the two different KT approaches. For the secondary research question (Objective 2.3) on the relative importance of KT predictors, a multiple linear regression [79,80] will be used to develop models of how years of practice, educational background, caseload characteristics, educational preferences, or Readiness to Change predict changes in knowledge, utilization, or integration following knowledge transfer interventions, with KT method as a covariate.

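### The first primary analysis is unadjusted and the ANCOVA omits four of the six factors on which the arms are balanced, which overstates the standard error of the between-group comparison of absolute scores

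*Protocol article*

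**What the plan says.** Under Group assignment procedure, the article describes a non-randomized allocation: "Subjects will be allocated using minimization within orthopedic and pediatric groups at each site". Within those strata it matches on four further variables: "We have identified pre-test scores, years of practice, practice area (urban/rural), and practice type (PT/OT) as the key predictors". The arms are therefore balanced on six factors: site, clinical area, profession, urban/rural setting, pre-test score and years of practice.

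Under Quantitative analyses, the first primary analysis is a two-way repeated measures ANOVA "to determine primary unadjusted differences in absolute scores over time, and between groups", run for knowledge, utilization and chart-stimulated recall. An ANCOVA of the same effects follows, "adjusting for baseline knowledge score, Readiness to Change, years of practice, and educational preference". Two of the six balancing factors are in that list. Site, clinical area, profession and urban/rural setting are in neither model.

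Elsewhere the article gives grounds to expect that some omitted factors matter. The Background says that use of outcome measures is low in orthopedic practice, while "within pediatric rehabilitation utilization levels are higher". Under Integration of knowledge, chart-stimulated recall is "conducted by a single trained research assistant assigned to each location", so any difference in rater severity falls on site.

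**The concern.** When arms are forced to be alike on a prognostic factor, that factor no longer adds to the variability of the arm difference. If the model leaves the factor out, its variance still counts in the residual. The estimated standard error then exceeds the true one, intervals are too wide and the test rejects less often than its nominal level. The precision that the matching was meant to buy is not collected.

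This is not a detail that a protocol leaves to an analysis plan. The article fixes which analysis comes first and lists the covariates, and that list does not follow the allocation. Because allocation is not randomized and 10% dropout is allowed for, any imbalance that remains on the four omitted factors would also go uncorrected in both models.

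**Working it through.** **Inputs from the article (Sample size requirements).** Two-sided type I error 0.05; standardized effect 0.50; 64 per group; 10% dropout; 144 therapists in three sites; in each site 24 per intervention, in three tutorial groups of eight, two orthopedic and one pediatric. The article prints "Type II error = 0.80"; its figures reproduce only if 0.80 is read as power.

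**The plan's own figure.** The normal approximation gives 63 per group. The exact t-test gives power 0.795 at 63 and 0.801 at 64, so 64 is right. 2 × 64 = 128, and 128/0.9 = 142.2, raised to 144 in the plan. The calculation assumes no covariate adjustment.

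**Assumed input.** R² is the share of outcome variance explained by the omitted factors. The article gives no value; 0 to 0.30 is shown. As a yardstick, a 2:1 orthopedic-to-pediatric mix and an assumed gap of D within-area standard deviations give R² = (2/9)D² / (1 + (2/9)D²). For D = 1 this is 0.222/1.222 = 0.18 from clinical area alone; for D = 0.5 it is 0.056/1.056 = 0.05.

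**Formulas, for one score compared between balanced arms with no clustering.** Let s = √(1 − R²).
- Width of the unadjusted interval relative to the adjusted one: 1/s.
- True type I error of the unadjusted test: 2[1 − Φ(1.96/s)].
- Unadjusted power: 1 − Φ((1.96 − m)/s), with m = 0.5 × √(64/2) = 2.83.
- Adjusted power: noncentral t with effect 0.5/s and 126 − 5 = 121 degrees of freedom. The five are two for site and one each for area, profession and setting.

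| R² | Width ratio | Type I error, unadjusted | Power, unadjusted | Power, adjusted |
|---|---|---|---|---|
| 0 | 1.00 | 0.050 | 0.81 | 0.80 |
| 0.10 | 1.05 | 0.039 | 0.82 | 0.84 |
| 0.20 | 1.12 | 0.028 | 0.83 | 0.88 |
| 0.30 | 1.20 | 0.019 | 0.85 | 0.92 |

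A simulation of 144 therapists balanced on the four factors (10,000 runs, R² = 0.20) agrees: interval width 0.659 unadjusted and 0.589 adjusted, type I error 0.028 and 0.046, power 0.87 and 0.91. Power is higher than in the table because no one drops out.

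**The group-by-time contrast.** A therapist's change score is the later score minus the earlier one. A factor that shifts both scores equally drops out of that difference, so omitting it costs nothing. In a simulation with two time points, stable factor effects, R² = 0.20 and a pre-post correlation of 0.5 given the factors, type I error was 0.047, interval width 0.589 and power 0.918, with or without the factors. The loss returns only if the factors predict change.

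**Clustering.** There are 3 sites × 2 arms × 3 groups = 18 tutorial groups, and neither model has a term for them. With an assumed intraclass correlation of 0.05 and R² = 0.20, simulations of a single score that differ in detail put the unadjusted type I error at about 0.05 to 0.07. Adding the factors but still no group term raises it to about 0.09 to 0.11.

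**The case against.** The strongest reply is that the planned lead analysis is a repeated measures ANOVA, and that the differential effect of the two interventions is its group-by-time term. Both pieces of evidence that the omitted factors matter are of the stable kind. Higher pediatric use is a difference in level, and a rater who scores every occasion at a site adds a constant. Such effects cancel in change. This stands, and it limits the point. It does not remove it, because the same sentence also plans a comparison of absolute scores between groups, where nothing cancels. Cancellation also needs an earlier measurement of each outcome. The article describes chart audit and recall under its post-intervention evaluations, although an analysis over time implies more than one occasion.

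Second, the size rests on an assumed R². This also stands: at R² = 0 nothing is lost. Standardized training and a scoring manual may also reduce rater differences between sites. But the article itself calls profession and urban/rural setting key predictors.

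Third, an ANCOVA is already planned, so which model leads may look like a matter of reporting order. Order alone would be a minor point; the four factors are missing from both models.

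A reader might infer more than this in three ways:
- **That the trial is underpowered.** It is not on this account. The unadjusted test still has at least the planned 80%; the loss is against an analysis that follows the design.
- **That the planned tests are below their nominal level overall.** This is not established. Unmodelled tutorial groups work in the opposite direction, and the net effect depends on two quantities that the article does not give.
- **That the loss is far larger for knowledge, because the pre-test is ignored as well.** It is not ignored. The screening test forms the baseline score, so it is a time level in the ANOVA, and it is a covariate in the ANCOVA.

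**Conclusion.** The point holds for the between-group comparison of absolute scores, and for change only if the omitted factors predict change. Allocation and analysis do not match: six factors are balanced, the first primary analysis carries none of them as covariates, and the ANCOVA carries two.

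For R² between 0.10 and 0.30 and no clustering, the cost is an interval 5 to 20% too wide, a true type I error of about 0.04 to 0.02, and 2 to 7 percentage points of power at an effect of 0.5. These figures depend on the assumed R². They describe this omission alone and not the net error rate of the trial, which also depends on clustering. The mismatch does not invalidate the trial, but it gives away precision that the design has already provided for.

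**What to change.** Make the adjusted model primary for each of the three outcomes. Its terms should be arm, site, clinical area, profession, urban/rural setting, baseline knowledge and years of practice, with Readiness to Change and educational preference as already planned. Report the unadjusted result as supportive.

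Fit this model with a term for tutorial group, as a random effect or an equivalent method, and let the degrees of freedom for the arm comparison reflect the 18 groups. The two changes belong together, because adding the factors without the group term would move the type I error further above nominal if outcomes are correlated within groups.

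The cost is a change of wording in the analysis section and five model degrees of freedom out of about 126, besides the group term. The balancing factors are known at allocation, so no new data are needed. If outcomes do cluster, the group term will widen intervals, but that width reflects the way the interventions are delivered.

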
Knowledge transfer interventions should bring knowledge into action. Constructivist principles recognize that knowledge is, "not a thing to be sent, but a fluid set of understandings shaped by both those who originate it and by those who use it" [52]. The user is seen as an active problem solver and a constructor of his/her own knowledge rather than a receptacle of information [52]. Clinicians must be able to use outcome measures within a valid and practical framework. Knowledge transfer strategies that engage researchers and clinicians to resolve these competing requirements may be more successful in facilitating the use of outcome measures. The possession of knowledge does not mean that it will be used. The need to go beyond dissemination that simply reflects successful distribution towards effective dissemination that requires use of the information has been emphasized [53]. Huberman [52] differentiated *conceptual use of knowledge*, which is characterized by changes in knowledge, understanding or attitude, from *instrumental use *that includes changes in behavior and practice. Practice surveys indicate both conceptual and instrumental knowledge deficits exist in musculoskeletal and pediatric practice [54]. Knowledge transfer interventions must target and assess both.

McMaster University has a worldwide reputation for educational innovation and problem-based learning (PBL). PBL is an ideal pedagogical strategy for facilitating knowledge transfer. Research on memory suggests memory and learning can be enhanced by: maximizing the positive effects of context by closely matching the learning and clinical environments, enhancing meaning by activating relevant prior knowledge, using educational activities that require the participants to elaborate on their information, and ensuring that new knowledge is used repeatedly in a number of different contexts [55]. The elaboration of information that occurs in tutorial discussion, the use of problems to match new knowledge to the clinical context, and the activation of prior knowledge have been recognized as active components of PBL [56]. Therefore PBL helps in the contextualization of knowledge and in the application of knowledge, which are key components of the CIHR knowledge transfer model (listed as KT3 and KT5 by CIHR).

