### Study measures

#### Baseline measurement of eligibility, status, and potential KT predictors

Participants will be pre-screened to ensure inclusion criteria. Eligible participants will then complete a baseline knowledge pre-test (to avoid ceiling effects/lack of responsiveness). Participants also will complete a baseline information questionnaire to collect demographic data, practice patterns, and educational background. Survey measures of knowledge and behavior will be administered. This data collection also will include a measurement of the therapist's intent to use outcome measures, their general level of research utilization, and their readiness to change. This scale evaluating Readiness to Change [40,41,73] was developed to reflect the core elements of the five stages of change, but was specifically applied to changing clinical practice. Although all participants will have agreed to allocation during informed consent, they will be asked their preference with respect to e-PBL and SHIPS so that post-hoc analyses can determine the importance of educational preference as a mediator of response.

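### The ANCOVA gives utilization and chart-stimulated recall a knowledge baseline instead of their own, so prior use is adjusted for only in part

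*Protocol article*

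**What the plan says.** The Quantitative analyses section first plans a two-way repeated measures ANOVA, over time and between groups, for knowledge, utilization and chart-stimulated recall. It then states: "An analysis of covariance will be used to compare these same effects adjusting for baseline knowledge score, Readiness to Change, years of practice, and educational" (the quote breaks off at its last item, the preferred course format). The list is written out and applies to all three outcomes alike.

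The section on baseline measurement says that "Survey measures of knowledge and behavior will be administered" and that the baseline collection covers the therapist's "intent to use outcome measures, their general level of research utilization, and their readiness to change". Of these, Readiness to Change and the knowledge score reach the ANCOVA. The surveyed behavior, the intent to use and the research utilization do not.

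The Group assignment procedure is explicitly non-randomized. It minimizes on pre-test score, years of practice, urban or rural practice and profession, within orthopedic and pediatric groups at each site. Prior use of outcome measures is not a factor.

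Chart audit and chart-stimulated recall are described under post-intervention evaluations, and the Abstract places the primary evaluations at 6 months. No baseline audit or recall is stated.

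**The concern.** Adjusting an outcome for its own earlier value is usually the most useful adjustment available. Here only the knowledge test gets it. The other two primary outcomes are adjusted for a knowledge score, and the Background warns against treating the two as the same: "The possession of knowledge does not mean that it will be used". It also reports that agreement with the need for outcome measures is high while their use is low. On the protocol's own reasoning, baseline knowledge is a weak stand-in for prior use.

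Two things are at stake for utilization and chart-stimulated recall. One is precision that a baseline could supply. The other is confounding: without randomization, a difference between the arms in prior use would carry over in part into the 6-month comparison. Two of the four ANCOVA covariates, knowledge and years of practice, are already balanced by the allocation, while prior use is addressed directly in neither place.

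**Working it through.** **Inputs from the protocol article (Sample size requirements).** "Assuming Type I error = 0.05 (2-tailed"); "Type II error = 0.80; Effect size = 0.50, the sample size required per group = 64"; the target is "detecting an effect of 0.50 between groups on any of the three aspects of outcome (knowledge, utilization, and integration into clinical reasoning"); "The sample size required for two-comparison groups = 128 and accounting for a 10% dropout = 128/0.9 = 142", rounded up to 144. The 0.80 has to be read as power, because only then does 64 per group follow.

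**The plan's own figure.** A two-sided t-test with effect 0.50 and power 0.80 needs 63.77, so 64 per group. Power at 64 is 0.801 (0.807 by the normal approximation used below). 128/0.9 = 142.2. The figure reproduces, and it assumes no covariate adjustment.

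**Assumptions.** The article gives no correlations. Let r be the correlation of the added baseline with the 6-month outcome, k that of baseline knowledge with the outcome (0.2 to 0.3), and c that between knowledge and the added baseline (0.2 to 0.4).

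**Precision beyond baseline knowledge.** Residual variance with knowledge alone is 1 − k². With both it is 1 − (k² + r² − 2krc)/(1 − c²). Two examples:

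- k = 0.3, c = 0.4, r = 0.3: 1 − (0.09 + 0.09 − 0.072)/0.84 = 0.871, against 0.91. The fall is 4%.
- k = 0.2, c = 0.2, r = 0.5: 1 − (0.04 + 0.25 − 0.04)/0.96 = 0.740, against 0.96. The fall is 23%.

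Power is Φ(0.50/√(2f/64) − 1.96), with f the residual variance. Over the assumed ranges:

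| r | fall in residual variance | power, knowledge only | power, both |
|---|---|---|---|
| 0.3 | 4-7% | 0.82-0.84 | 0.85-0.87 |
| 0.5 | 19-23% | 0.82-0.84 | 0.90-0.92 |

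**Counting Readiness to Change as well.** Set every correlation, with the outcome and among predictors, to 0.3. For m predictors R² = 0.09m/(1 + 0.3(m − 1)), giving 0.090, 0.138 and 0.169 for m = 1, 2, 3. Adding behavior to knowledge alone cuts the remaining variance by (0.138 − 0.090)/0.910 = 5.3%. Adding it to knowledge and Readiness cuts it by (0.169 − 0.138)/0.862 = 3.5%. Readiness takes up part of the gain.

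**Confounding.** With knowledge balanced between arms, an imbalance of 0.2 SD in prior use shifts the knowledge-adjusted difference by 0.2 × (r − kc)/(1 − c²). This is 0.04-0.05 SD at r = 0.3 and 0.09-0.10 SD at r = 0.5, or 9-11% and 18-20% of the 0.50 planning effect. It is smaller where Readiness to Change picks up the same imbalance. For scale, chance alone with 64 per arm allows 1.96 × √(2/64) = 0.35 SD in an unbalanced factor.

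**If a baseline audit and recall exist.** A change-type comparison has variance factor 2(1 − r), and an ANCOVA on the own baseline has 1 − r². At r = 0.3 these are 1.40 and 0.91 (power 0.67 and 0.84). At r = 0.5 they are 1.00 and 0.75 (power 0.81 and 0.90). The repeated measures analysis therefore does not make the covariate redundant.

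**The case against.** The strongest reply is that prior use is not left uncontrolled. Three parts of it stand.

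- Allocation is done within orthopedic and pediatric groups. The one difference in prior use that the Background reports is between these fields: low in orthopedic practice, higher in pediatric rehabilitation. That part is balanced by design.
- Readiness to Change is in the model, and its Action and Maintenance stages describe current behavior. It records a stage, though, not an amount of use, so it is a partial proxy.
- The repeated measures ANOVA would use an earlier value of each outcome if there were one. Its wording implies one, but the sections on utilization and integration describe only post-intervention measurement. This has to be settled first, and the answer decides which baseline the ANCOVA should use.

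A further reply is that the survey may be a poor substitute. It is self-report, the article does not say that its behavior items measure outcome-measure use, and nothing shows that it tracks a rated recall interview. That is fair. It argues for the lower values of r and for ranking the survey score second.

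A reader might infer a rise in power from 81% to 84-94% (r from 0.3 to 0.6), or a bias of 0.06-0.12 SD. Those figures compare the added baseline with no adjustment at all. The planned ANCOVA already has four covariates, so they overstate what is gained.

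**Conclusion.** The point holds as a limited one. The covariate list is a stated choice, and for two of three primary outcomes it omits a baseline of the outcome itself. Existing controls reach prior use in part, and differences between therapists within a field can remain.

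The gain rests on correlations that the article does not give. Beyond baseline knowledge it is about 4-7% of residual variance at r = 0.3, generally less once Readiness to Change is counted, and about 19-23% at r = 0.5. It becomes material only from about r = 0.5.

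Two stronger readings are not supported. The trial is not underpowered on this account, since 64 per group assumes no adjustment and keeps its 80%. Nor is prior use wholly uncontrolled, given the allocation within fields and the Readiness to Change covariate.

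**What to change.** In Quantitative analyses, keep the four listed covariates and make the baseline specific to each outcome:

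- Knowledge: baseline knowledge score, as now.
- Utilization and chart-stimulated recall: the outcome's own baseline, if chart audit and recall are done before the intervention.
- If they are not, the surveyed behavior score from the baseline questionnaire, after confirming that it captures use of outcome measures.

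State explicitly whether audit and recall are done at baseline. The repeated measures ANOVA needs that answer too, and adding the survey covariate would not supply the missing time point. Settle the wording before outcome data are seen.

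The cost is one or two model degrees of freedom and a change of text. No new data are needed if the survey score is used. A baseline audit and recall, if not already planned, would be extra fieldwork and is not required for this change to the ANCOVA.

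### The sample size fits a one-occasion comparison, but the first primary analysis is an unadjusted contrast over time; a 6-month comparison adjusted for each outcome's own baseline would secure the stated power

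*Protocol article*

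**What the plan says.** **Sample size requirements.** "Sample size estimation was based on detecting an effect of 0.50 between groups on any of the three aspects of outcome". The inputs are a two-sided 5% type I error and "Type II error = 0.80; Effect size = 0.50"; the 0.80 is evidently meant as power. The result is that "the sample size required per group = 64". Dropout is then added ("accounting for a 10% dropout = 128/0.9 = 142") and the total is rounded up to 144. The section also says "we expect to accommodate 24 participants per intervention group, per site", which over three sites is 24 × 3 = 72 per arm. It does not say which SD standardises the 0.50, and it mentions neither repeated measures nor a correlation over time.

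**Quantitative analyses.** The first primary analysis is an unadjusted two-way (group by time) repeated measures ANOVA of absolute scores, for each of knowledge, utilization and chart-stimulated recall. An ANCOVA then serves to "compare these same effects adjusting for baseline knowledge score, Readiness to Change, years of practice, and educational preference". The two together are to settle relative effectiveness, and effect sizes with 95% confidence intervals are to show "differential impacts on change in knowledge, utilization, and integration of knowledge between the two different KT approaches".

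**Timing and baseline data.** The Abstract places the primary evaluations six months after the intervention. The section on baseline measurement lists the knowledge pre-test and survey measures of knowledge and behavior. Chart audit and chart-stimulated recall are described only under the post-intervention evaluations.

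**The concern.** The calculation behind 64 per group and the analysis named first are different contrasts. A difference between arms at one occasion is measured against the SD of the score. A group-by-time test over two occasions is measured against the SD of change, which depends on the correlation r between the occasions. A given 6-month difference is therefore harder to detect on change than at 6 months alone when r is below 0.5, and easier when r is above it.

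The article gives no r. The chart-based outcomes sample little practice: five charts from one randomly chosen day for utilization, and two of those five for recall. If a baseline audit used the same design, that sampling noise would tend to lower r.

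The planned ANCOVA could remove the dependence on r, but its covariate list carries baseline knowledge for all three outcomes. Utilization and recall are not adjusted for their own baselines. At stake is how a null result on these two outcomes is read: it could reflect the choice of contrast and not similar performance of the two delivery modes.

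**Working it through.** **Inputs from the article:** two-sided alpha 0.05; power 0.80; effect 0.50; 64 per arm evaluable, 72 per arm enrolled. **Assumed, because the article does not state them:** 0.50 is in SDs of a single-occasion score; equal variances at both occasions; two occasions (baseline and 6 months); no arm difference at baseline; r from 0 to 0.7. Power is from the non-central t distribution for two independent groups.

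**1. The plan's own figure.** A two-sample t-test for an effect of 0.50 needs 63.8, so 64 per group, and power at 64 is 80.1%. The figure reproduces as a one-occasion comparison. (Read literally as a type II error of 0.80, i.e. power 0.20, it would need about 11 per group, so the printed label is a slip.)

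**2. Group-by-time test (change).** SD of change = SD × √(2(1 − r)), so the effect becomes 0.50/√(2(1 − r)). At r = 0.3 this is 0.50/√1.4 = 0.423; at r = 0.5 it is 0.50/√1 = 0.50.

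**3. Between-groups term of the same ANOVA.** Averaging over two occasions halves the difference to 0.25, and the SD of the average is √((1 + r)/2). At r = 0.3 the effect is 0.25/√0.65 = 0.310.

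**4. ANCOVA of the 6-month score on its own baseline.** Residual SD = SD × √(1 − r²), so the effect is 0.50/√(1 − r²). At r = 0.3 this is 0.50/√0.91 = 0.524.

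| r | Change, 64/arm | Change, 72/arm | Between-groups term, 64/arm | ANCOVA on own baseline, 64/arm | n per arm for 80% on change |
|---|---|---|---|---|---|
| 0 | 51% | 56% | 51% | 80% | 127 |
| 0.2 | 60% | 65% | 44% | 82% | 102 |
| 0.3 | 66% | 71% | 41% | 84% | 89 |
| 0.4 | 73% | 78% | 39% | 87% | 77 |
| 0.5 | 80% | 85% | 37% | 90% | 64 |
| 0.7 | 95% | 97% | 33% | 98% | 39 |

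**5. Threshold.** Power on change equals 80% at r = 0.498 with 64 per arm, and at r = 0.434 with 72 per arm.

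**6. Other basis for the 0.50.** If it is in SDs of change, the group-by-time effect is 0.50 whatever r is, and power at 64 per arm is 80.1% throughout.

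**7. Three occasions.** Knowledge is also re-tested immediately after the intervention. With three occasions and equal correlations between them, the 2-df group-by-time test at 64 per arm depends on the pattern of arm differences as well as on r. At r = 0.3 it has 69% for differences of 0, 0.5, 0.5 and 56% for 0, 0.25, 0.5. At r = 0.5 it has 84% and 71%.

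**The case against.** The strongest reply is that the 0.50 may already be an effect on change. Objective 1 is phrased in terms of changing the three outcomes, and the effect sizes to be reported are on change. On that reading 64 per group gives 80% at any r and there is no shortfall. This stands as a possible reading. The sample size section does not exclude it, although the ANOVA is described as one of absolute scores.

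Second, for knowledge the plan already contains the remedy. The ANCOVA adjusts for baseline knowledge and is one of the two analyses that settle relative effectiveness. Read as an adjusted comparison of follow-up scores, it is adequately powered at any r. This also stands. The wording leaves some doubt, since the ANCOVA is to compare the same effects as the ANOVA, which include time. Kept in that form, the pre-test would be both an outcome level and a covariate.

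Third, the article describes no baseline chart audit or recall. Without them r is undefined for those outcomes and the power figures for change do not apply. That is fair, but a repeated measures ANOVA over time on all three outcomes presupposes an earlier measurement. Either the baseline scores exist, or that analysis cannot be run for two of the three outcomes.

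Fourth, allocation pairs participants partly on similar pre-test scores, which the independent-groups formulas ignore. This bears mainly on knowledge and does not settle the other two outcomes.

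Finally, ANOVA on change and baseline-adjusted ANCOVA are both accepted methods. True, but only the ANCOVA on the outcome's own baseline has the stated power without an assumption about r.

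**Conclusion.** The point holds in conditional form. The stated size is for a one-occasion comparison, while the analysis named first is an unadjusted contrast over time whose power the sample size section does not establish. With 0.50 in single-occasion SDs, two occasions and equal variances, the group-by-time test at 64 per arm reaches 80% only for a correlation of about 0.5 or more. It has 66% at 0.3 and 60% at 0.2. With all 72 per arm evaluable the threshold is about 0.43.

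A reader might infer that the trial is underpowered, or that its 80% fails unless r is at least 0.5. The article does not support that: the SD basis of the 0.50 and the value of r are both unstated, and 80% holds at any r if 0.50 is in SDs of change. Nor does the ANCOVA fail throughout, because for knowledge it can supply the needed adjustment. The firm gap is in utilization and chart-stimulated recall, where the listed covariates omit the outcome's own baseline. This should be changed, because the remedy costs little.

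**What to change.** - **Primary contrast.** For each outcome, use the arm difference in the 6-month score from an ANCOVA adjusted for that outcome's own baseline, with baseline as a covariate only. For knowledge this is the pre-test. For utilization and recall it is the baseline audit and recall scores that the planned repeated measures ANOVA already presupposes.
- **Sample size section.** State that 64 per group refers to this 6-month contrast and that 0.50 is in SDs of the 6-month score.
- **Change analyses.** Keep the group-by-time results and the effect sizes on change as supportive.
- **If no baseline audit or recall is collected.** The over-time ANOVA cannot be run for those two outcomes. Compare their 6-month scores between arms, adjusting for the baseline survey measure of behavior, and do not claim the own-baseline power gains in the table.

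Cost: a change of analysis wording, no added participants, and no data beyond what the planned ANOVA needs. The downside is that the change analysis becomes supportive instead of primary, although Objective 1 is phrased in terms of change.
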